# Effects of Montmorency Tart Cherry and Blueberry Juice on Cardiometabolic Outcomes in Healthy Individuals: Protocol for a 3-Arm Placebo Randomized Controlled Trial

**DOI:** 10.3390/ijerph18189759

**Published:** 2021-09-16

**Keywords:** tart cherry, blueberry, cardiovascular disease, blood pressure, metabolic health

## Abstract

Cardiometabolic disease is recognized as the predominant cause of global mortality and healthcare expenditure. Whilst pharmaceutical interventions are effective in the short term, their long-term efficacy remain equivocal and their associated side-effects are concerning. Owing to their high levels of anthocyanins, Montmorency tart cherries and blueberries have been cited as potentially important natural treatment/preventative modalities for cardiometabolic disease. This study proposed a randomized controlled trial, aims to test the effects of consumption of Montmorency tart cherry and blueberry juice on cardiometabolic outcomes compared to placebo. This 20-day, parallel, single-blind, randomized, placebo-controlled trial will recruit 45 individuals, who will be assigned to receive 60 mL per day of either Montmorency tart cherry juice, blueberry juice or a cherry/blueberry flavoured placebo. The primary study outcome is the between-group difference in systolic blood pressure from baseline to post-intervention. Secondary outcome measures will be between-group differences in anthropometric, energy expenditure and substrate oxidation (during rest and physical activity), haematological, blood pressure/resting heart rate, psychological wellbeing and sleep efficacy indices. Statistical analysis will be conducted on an intention-to-treat basis. This study has been granted ethical approval by the University of Central Lancashire, Health Research Ethics Committee (ref: HEALTH 0016) and formally registered as a trial. Dissemination of the study findings from this investigation will be through publication in a leading peer-reviewed journal.

## Strengths and Limitations of this Study

-This study will be the first randomized placebo-controlled trial to examine the effectiveness of both Montmorency tart cherry and blueberry juice on cardiometabolic outcomes.-Primary and secondary outcomes measures are central to the treatment of cardiometabolic disease and its comorbidities.

## 1. Introduction

Cardiovascular conditions, type 2 diabetes mellitus and other associated cardiometabolic disease modalities are recognized as the predominant causes of global mortality and healthcare expenditure [1]. Cardiometabolic syndrome is characterized by a range of symptoms including hypertension, obesity, insulin resistance, atherogenic dyslipidaemia, low high-density lipoproteins, high triglycerides, high levels of adiposity, high body mass index, large waist to hip ratio and poor glucose regulation [2]. To date, different pathophysiological biomarkers have emerged within the literature, with indices of oxidative stress, nitric oxide and inflammation being cited as key mechanisms that promote the clinical manifestation of cardiometabolic disease [3,4].

Traditional treatment modalities for cardiometabolic disease habitually include angiotensin-converting enzyme inhibitors, betablockers, calcium antagonists, diuretics, and lipid-lowering drugs [5]. However, whilst administration of these medications is effective in the treatment, postponement and prevention of cardiometabolic disease, their longitudinal effects and cost-effectiveness has yet to be corroborated [6], and significant negative side-effects remain common [7]. These side effects paired with recent findings show that globally 84% of adults over the age of 57 are currently taking at least one prescription medication per day and emphasize that natural cost-effective remedies are necessary for the management of cardiometabolic disease [8].

The efficacy of improved habitual dietary practice on cardiometabolic health is unambiguous, to the extent that medical organizations recommend this as the primary approach for the prevention and management of cardiometabolic disease [9]. This therefore provides a clear rationale for the adoption of dietary interventions; and indeed, moderate and sustainable improvements in health, based around effective nutritional approaches are more noteworthy, cost-effective and safer than ‘high risk’ pharmacological drugs consumed in the short-term to treat and prevent metabolic disease [10]. Diets rich in fruits and vegetables have been shown to provide protection from cardiometabolic disease [11]. However, establishing and maintaining a dietary pattern high in fruits and vegetables over a sustained duration is difficult to accomplish [12]; therefore, dietary supplementation represents a potentially more appealing treatment and prevention modality.

Anthocyanins are abundant in many fruits and vegetables and impart the dark colours found in various fruit and vegetable groups [13]. There is growing evidence that anthocyanins may confer significant improvements to cardiometabolic health [14] and Montmorency tart cherries, blueberries, strawberries, cranberries and blackcurrants (i.e., dark fruits) [15] in particular have been shown to possess high anthocyanin contents [16], although the majority of peer-reviewed literature has focused on tart cherries. Importantly, supplementation of anthocyanin rich tart cherries has been shown to effectively combat oxidative stress [17,18] and inflammation [18,19,20] and that blackberry supplementation promotes increased fat oxidation rates [21]. Improved fat oxidation rates during rest and physical activity are linked to long-term changes in body mass and composition allied to improvements in insulin sensitivity [22]. Therefore, an increased capacity to oxidize fat at rest and during moderate physical activity, instigated via anthocyanin rich supplementation, may be advantageous for yielding improvements in body composition and insulin control. Importantly, the aforementioned anti-inflammatory, anti-oxidative and substrate trafficking effects, mediated through supplementation of anthocyanin rich fruits, conveniently target the underlying chronic low-grade inflammation, pro-oxidant and lipid attenuating status that is central to cardiometabolic pathophysiology [23].

However, the findings from parallel trials investigating the effects of anthocyanin rich fruit supplementation on cardiometabolic outcomes have yielded equivocal findings. Some studies exploring the effects of tart cherry juice supplementation have shown no effect on cardiometabolic indices of blood pressure, triglycerides, insulin tolerance or cholesterol [24,25,26,27] and some have revealed improvements in systolic blood pressure and low-density lipoprotein (LDL) cholesterol [28,29]. Studies exploring the efficacy of other anthocyanin rich supplements present a similarly equivocal picture, with some demonstrating positive effects on cardiometabolic outcomes [30,31,32,33,34] and some showing no such effects [35,36,37,38]. At the current time, there has yet to be any randomized intervention studies, comparatively examining the efficacy of different anthocyanin rich fruit supplements on cardiometabolic outcomes. With some food biochemical investigations showing that anthocyanin contents in dark fruits such as blueberries are as high or even greater than in tart cherries [16], further such investigations may be of both practical and clinical relevance.

### 1.1. Aims and Objectives

The aim of the current study was to investigate the influence of 20 days of twice daily Montmorency tart cherry or blueberry juice supplementation on cardiometabolic health indices in healthy adults compared to placebo. The primary objective of this randomized trial is to examine the influence of the tart cherry and blueberry supplements on systolic blood pressure relative to placebo. Its secondary objectives are to assess if tart cherry juice and blueberry supplementation impacts on other risk factors for cardiometabolic disease.

### 1.2. Hypotheses

In relation to the primary outcome, both Montmorency tart cherry and blueberry supplement groups will mediate reductions in systolic blood pressure compared to the placebo, but no differences will be observed between supplement groups. Furthermore, for the secondary outcomes, the Montmorency tart cherry and blueberry groups will produce improvements in cardiometabolic health parameters compared to the placebo, but there will be no differences between the two supplement groups.

## 2. Materials and Methods

Described according to the updated guidelines for reporting parallel group randomized trials [39].

### 2.1. Study Design and Setting

This investigation represents a 20-day parallel, single-blind (blinded to participant) randomized placebo-controlled trial (Figure 1). After screening for eligibility and enrolment, participants will be familiarized with the testing equipment, questionnaires and procedures. Participants will then be randomized by a computer program (Random Allocation Software) to either a Montmorency tart cherry, blueberry or placebo group. Cardiometabolic health and other variables, as described in detail below, will be assessed at baseline and after 20 days (post-intervention). In agreement with previous trials of cardiometabolic health, the primary outcome measure will be the between-group difference in systolic blood pressure from baseline to post-intervention [27]. Secondary outcome measures will be between-group differences in anthropometric, energy expenditure and substrate oxidation (during rest and physical activity), haematological, blood pressure/resting heart rate, psychological wellbeing and sleep efficacy indices. All experimental visits will take place in the morning and be undertaken in a ≥10 h fasted state. Participants will also be required to arrive hydrated and to avoid strenuous exercise, alcohol, and nutritional supplements for 24 h and caffeine for 12 h prior.

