### 2.3. Recruitment

It is expected that participants will predominantly be recruited from the UK city of Preston and its surrounding areas. Recruitment will be undertaken by poster promotion across the university campus, at local workplaces and also through advertisements on social media. Interested individuals will be able to contact the research team for further study information and to ask any questions associated with participation in the study. Participants will be invited to attend an eligibility, enrolment and familiarization session at the University of Central Lancashire. Written informed consent will be obtained from those willing to take part.

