### 2.4. Dietary Intervention

After the conclusion of their baseline data collection session, participants will be provided with either Montmorency tart cherry, blueberry or placebo concentrate. Participants will be required to consume 30 mL of supplement diluted in 100 mL of water twice daily: once in the morning and again in the evening [27]. All supplementations will be kept refrigerated throughout. According to the manufacturer (ActiveEdge, Hanwell, UK), a 30 mL dose of Montmorency tart cherry concentrate (energy: 102 kcal, carbohydrates: 25 g of which sugars: 18 g, protein: 1.10 g and fibre: 2.6 g) is equivalent to approximately 320 mg of anthocyanins. Similarly, taking into account the manufacturers (ActiveEdge, Hanwell, UK) guidelines, a 30 mL dose of blueberry concentrate (energy: 103 kcal, carbohydrates: 22 g of which sugars: 22 g, protein: 0.2 g and fibre: 0.2 g) is equivalent to approximately 387 mg of anthocyanins. Preparation of the placebo will involve mixing 100% un-flavoured maltodextrin carbs (MyProtein, Cheshire, UK) into drinking water using a magnetic stirrer (Stuart Scientific, UK) and stir bar (Fisher Scientific, Waltham, MA, USA). Then, 666 g of maltodextrin will be added to water to create a litre of placebo concentrate, working out as 20 g of maltodextrin per 30 mL serving, closely matching the Montmorency tart cherry or blueberry concentrates. Even amounts of red and black food colouring will be added to match the colour of the Montmorency tart cherry concentrate and even amount of red, blue and black colouring to match the colour of the blueberry supplement. Either cherry or blueberry flavdrops (1 mL) (MyProtein, UK) will then added to match the required flavour. A 30 mL dose of placebo concentrate (100 kcal, carbohydrates 25 g of which sugars: 0 g, protein: 0 g and fibre 0 g) contains 0 mg of anthocyanins. This method of placebo preparation has been shown by previous intervention trials to provide an effective blinding strategy [42].

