### 2.5. Data Collection

#### 2.5.1. Laboratory Visit Data

All measurements will be made at University of Central Lancashire’s physiology laboratory and will be undertaken in an identical manner on two occasions, i.e., baseline and post-intervention. The laboratories housed by the University of Central Lancashire are fully accredited by the British Association for Sport and Exercise Sciences, illustrating that they have undergone meticulous inspection and evidenced that; all instrumentation is well maintained in terms of reliability, validity and routine servicing, staff have the appropriate professional and vocational qualifications and that the requisite operational procedures for health and safety are met.

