### 2.7. Statistical Analysis

All experimental data (with the exception of the subjective ratings of trial arm allocation) will be continuous and will therefore be presented as mean and 95% CIs. Statistical analysis of all baseline variables will be conducted to compare the three groups at baseline using linear mixed models, with groups modelled as a fixed factor and random intercepts by participants. All analyses of the intervention-based data will be performed using an intention to treat basis, and all randomized participants will be included in the final analysis as far as data collected will allow. Furthermore, in order to determine the effects of the intervention on all of the outcome measures, differences between the three groups will be examined using linear mixed models with group modelled as a fixed factor and random intercepts by participants adopted, adjusted for baseline values modelled as a continuous fixed covariate. For linear mixed models the mean difference (*b*), *t*-value and 95% confidence intervals of the difference will be presented. Finally, blinding efficacy will also be examined using a chi-squared (*Χ*^2^) test. All analyses were conducted using SPSS v27 (IBM, SPSS), and statistical significance for all analyses was accepted as the *p* ≤ 0.05 level.

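### As described, participants are randomised before the baseline session and only they are blinded, so measuring staff can know the arm at both visits; moving allocation and coding the product would close this cheaply

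*Protocol article*

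**What the plan says.** All references are to the protocol article.

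- **Who is blinded.** Section 2.1 calls the study a "single-blind (blinded to participant) randomized placebo-controlled trial". No section extends the blind to the staff who measure, and the blinding check in section 2.4 questions participants only.
- **Order of steps.** Section 2.1 begins: "After screening for eligibility and enrolment, participants will be familiarized with the testing equipment, questionnaires and procedures". The next sentence opens "Participants will then be randomized by a computer program", and assessment at baseline and after 20 days is mentioned after that. Section 2.3 describes the first attendance: "Participants will be invited to attend an eligibility, enrolment and familiarization session at the University of Central Lancashire". It lists no baseline measurement there.
- **Measurement occasions.** Section 2.5.1 says that all measurements "will be undertaken in an identical manner on two occasions, i.e., baseline and post-intervention".
- **When product is supplied.** Section 2.4: "After the conclusion of their baseline data collection session, participants will be provided with either Montmorency tart cherry, blueberry or placebo concentrate". Unused product comes back to the laboratory at the post-intervention session.
- **Use of the baseline value.** In section 2.7 the model for every outcome is "adjusted for baseline values modelled as a continuous fixed covariate". All randomised participants are to be analysed so far as the data permit.

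**The concern.** Two features combine. Allocation, as narrated, exists before baseline is measured, and nothing keeps it from the people who measure. The baseline value can then no longer be assumed free of any influence of the arm, and it enters every adjusted comparison as a covariate. The post-intervention value is open to the same influence, and returned product arrives at that very visit.

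The hypotheses in section 1.2 are directional: both juices are expected to beat placebo. Staff who know the arm could, without intending to, vary positioning, conversation, tape placement or instructions.

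There is also a smaller matter of completeness. A participant who is randomised but lost before the baseline session has no covariate and cannot enter the adjusted model, although section 2.7 aims to include everyone randomised. Nothing in the design as described makes that loss necessary.

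**Working it through.** **1. The plan's own figure.** The point does not depend on the sample size, but the figures set the scale. Inputs from section 2.2.3: difference 6 mmHg, SD 5.5 mmHg, power 80%, loss 10%. Alpha is 0.05 (section 2.7), taken as two-sided.

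n per arm = 2 × (1.960 + 0.842)² × (5.5/6)² = 13.19. Dividing by 0.9 gives 14.7, so 15 per arm and 45 in three equal arms. The stated total is reproduced and is not in question here.

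**2. The sequence.**

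| Step | Section | Needs the allocation? |
|---|---|---|
| Eligibility, enrolment, familiarisation | 2.1, 2.3 | No |
| Randomisation | 2.1 | – |
| Baseline session | 2.1, 2.5.1 | No |
| Supply of product | 2.4 | Yes |
| Post-intervention session, return of product | 2.4, 2.5.1 | No |

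The first step that needs the allocation is supply of product. Randomisation is placed one step earlier than necessary.

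**3. How an arm-related error would pass through the model.** Let e_base and e_post be systematic errors in the recorded values of one arm relative to placebo, and β the within-arm slope of outcome on baseline. Then

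shift in adjusted difference = e_post − β × e_base.

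The documents give none of these quantities. For illustration only, take errors of 1 mmHg and β between 0.5 and 0.9:

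| Assumed error (mmHg) | Shift (mmHg) | Absolute shift as share of 6 mmHg |
|---|---|---|
| Baseline only, +1 | −0.5 to −0.9 | 8% to 15% |
| Post-intervention only, +1 | +1.0 | 17% |
| Both visits, same direction, +1 and +1 | +0.5 to +0.1 | 8% to 2% |
| Opposite directions, baseline +1, post −1 | −1.5 to −1.9 | 25% to 32% |

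The result depends on the pattern assumed. An equal error at both visits largely cancels, whereas opposite errors add.

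**4. Effect on a test against placebo, also illustrative.** With 15 × 0.9 = 13.5 completers per arm, the standard error of a difference is 5.5 × √(2/13.5) = 2.12 mmHg. On a two-sample t-test, a systematic error of 1, 2 or 3 mmHg in the post-intervention reading would raise the two-sided type I error from 5% to about 7%, 15% or 28%. Nothing in the article suggests that errors of these sizes would occur.

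**5. What limits the route for systolic pressure.** Section 2.5.5 prescribes an automated monitor and three readings one minute apart, and analyses the mean of the last two. The readings follow the resting energy test, which section 2.5.3 sets at 20 minutes supine. Section 2.5.1 requires the same procedure on both occasions. Little is left to the observer. Waist and hip circumference (section 2.5.2) depend on where and how a person places a tape, and have less protection.

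**The case against.** The strongest reply is that the order is inferred from a condensed overview. The sentence about baseline and 20 days names the occasions and does not expressly say that both follow randomisation. Section 2.4 is compatible with an allocation generated early and disclosed only when product is handed over. Figure 1 might settle this, but it is not shown. Who generates and holds the list is detail that an article commonly leaves to the full protocol. This stands as a limit: the text shows that staff can know the arm, not that they do. It does not remove the point. Participant-only blinding is stated outright, and disclosure at supply would protect the baseline visit but not the post-intervention one.

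The second reply is that the primary outcome is well protected by the device and the fixed procedure, that the walking test is set at a fixed speed and duration, and that the questionnaires are answered by blinded participants. This largely stands, and is why the risk to systolic pressure is modest.

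A reader might infer that the baseline covariate is biased, and that the primary comparison is off by 8% to 15% of the 6 mmHg difference. The documents do not support this. The 1 mmHg error and the slope are both assumptions, no source for an error of that size with an automated monitor is given, and the same error at both visits would mostly cancel.

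The loss before baseline is also unquantified. Section 2.2.3 allows 10% loss overall (4.5 of 45) without saying when it occurs, and section 2.7 already concedes that missing data may limit inclusion.

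**Conclusion.** The point holds as a design weakness that is cheap to remove. On the article's own account, allocation precedes baseline without need, and nothing withholds the arm from measuring staff at either visit. The risk is modest for systolic pressure and greater for measures that depend on the operator, with circumferences the clearest case. No size of bias follows from the documents, and the figures in mmHg show sensitivity only. The trial is not invalidated and the sample size is unaffected.

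The conclusion rests on reading section 2.1 as chronological and on there being no staff masking beyond what the article states. If the full protocol already withholds the arm at both visits, a sentence saying so is all that is needed.

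**What to change.** 1. Generate or reveal the allocation only after a participant's baseline session is complete, immediately before product is supplied. Each randomised participant who completes that session then has the covariates the model needs.
2. Issue all three products in matched containers labelled with participant codes. The juices are manufacturers' concentrates and the placebo is mixed locally, so labels alone would not be enough.
3. Have an existing team member who takes no measurements hold the code and receive and measure returned product, so that those taking post-intervention measurements do not learn the arm.
4. State these arrangements in section 2.1. If they are already in place, only the statement is needed.

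Step 1 protects the baseline value only; steps 2 and 3 are needed for the post-intervention visit. The cost is some repackaging and separation of tasks within the present team. No extra participants, visits or equipment for measurement are required.

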### 2.2. Participants

#### 2.2.1. Inclusion Criteria

-Eighteen years of age and above-Non-smoker-BMI < 30-Able to give informed consent

#### 2.2.2. Exclusion Criteria

-Pregnancy-Sixty-five years of age and above-Diabetes or any other metabolic/uncontrolled hypertensive conditions-Food allergies to cherries or blueberries-Habitual consumption of blueberries/cherries and/or blueberry/cherry products-Not regularly taking medication or antioxidant supplements

